### Patient groups

DMPs target different patient populations, including CVD (9 DMPs), chronic obstructive pulmonary disease (COPD) (5), diabetes (3), heart failure (1), stroke (1), depression (1), psychotic diseases (1) and eating disorders (1). To evaluate the effectiveness of DMPs in real-life settings, we will enrol a broad and representative sample of patients from each DMP. All patients in the DMP will be eligible to participate in the evaluation and no additional inclusion criteria beyond that of the DMPs will be applied [15]. Written informed consent will be obtained from all participants.

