**Clinical outcomes**		
HbA1c (diabetes)	Medical registries	%
Glucose (diabetes/CVD)	Medical registries	mmol/l
Blood pressure (diabetes/CVD/heart failure)	Medical registries	mmHg
Lipids (diabetes/CVD)	Medical registries	
LDL		mmol/l
Total cholesterol		mmol/l
FEV_1 _(COPD)	Medical registries	%
FEV_1_/FVC (COPD)	Medical registries	
Exacerbations (COPD)	Medical registries	
BDI (depression)	Medical registries	

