### Data analysis

We will explore the effects of DMPs by monitoring their implementation differences. Descriptive statistical analysis will be performed on patient demographics and other study variables, such as combinations of interventions or programme implementation. In order to evaluate the costs and effects of the disease management interventions on the primary outcomes at the patient, professional and organisational levels, we will compare changes in outcome measures at T2, T3, and T4 between DMPs and within programmes between intervention and controls. Primary outcomes in terms of functional status and QoL will be estimated after correction for potential confounders and differences in starting values between the treatment groups or projects. Changes in generic health outcome measures (SF-36, EQ-5D), number of disease episodes (flare-ups), and patient experiences will be comparable across projects with recognition to the fact that the episodes' nature and impact varies across diseases. The primary clinical outcomes (e.g., lung function, cholesterol level) as extracted from medical records are to some extent made comparable across projects by expressing them in number of patients with a 'minimal clinically important' improvement.

All data will be analysed according to intention-to-treat principles in which data from all subjects are used regardless of the subjects' adherence to protocol. To account for missing costs and health outcomes due to incomplete projects and the uncertainty so introduced, we will perform sensitivity analyses using various imputation techniques.

The relation between a DMP's total costs and the estimated health outcome changes is expressed in cost-effectiveness ratios. Examples are costs (1) per QALY, (2) per additional patient with a minimal clinically relevant improvement in QoL, (3) per additional patient with a clinically relevant improvement in the clinical outcome measure, and (4) per disease episode prevented. Uncertainty around cost-effectiveness will be dealt with by bootstrapping costs and health outcomes, plotting them on cost-effectiveness planes, and drawing cost-effectiveness acceptability curves.

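### The cross-project count of clinically improved patients, and the cost-effectiveness ratio built on it, cannot tell stable patients from worsened ones, so they respond less to prevented deterioration

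*Protocol article*

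**What the plan says.** The Data analysis section of the protocol article takes "The primary clinical outcomes (e.g., lung function, cholesterol level) as extracted from medical records" and says that they are, to some extent, "made comparable across projects by expressing them in number of patients with a 'minimal clinically important' improvement". Example ratio (3) in the same section is cost "per additional patient with a clinically relevant improvement in the clinical outcome measure". Neither has a category for staying stable or for a decline avoided.

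The section also contains measures that can credit prevention:
- a general comparison, in which "we will compare changes in outcome measures at T2, T3, and T4 between DMPs and within programmes between intervention and controls";
- the statement that "Changes in generic health outcome measures (SF-36, EQ-5D), number of disease episodes (flare-ups), and patient experiences will be comparable across projects";
- ratio (1), cost per QALY;
- ratio (4), cost "per disease episode prevented".

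Table 1 lists FEV1 (in %), FEV1/FVC and exacerbations as clinical outcomes for COPD. The Patient groups section gives COPD 5 of the 22 programmes. The Research methods section says that the main comparison is between programmes and that most have a pre-post design internally. Seven have late-starter controls delayed by one year, and two randomise patients.

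**The concern.** The count is meant to put clinical results from different diseases on one scale. It records only movement in one direction. If the usual course of a measure is downward over the two years, part or most of a programme's benefit lies in fewer patients getting worse, and the count does not record that. For a measure that can be corrected, such as cholesterol, the benefit lies in the direction that is counted. Part of a difference between programmes could then reflect the direction of the measure and not the programme.

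The design adds to this. With 7 delayed-start and 2 randomised programmes, at least 22 − 7 − 2 = 13 have no stated concurrent control. In those, no untreated group shows what decline would have occurred, and the improved share is all the reader sees on this scale. Ratio (3) carries the same gap into the economic evaluation.

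**Working it through.** **Inputs.** The article states no threshold, SD, rate of decline, sample size or power, so there is no figure to reproduce. Everything numerical below is an assumption. I work in units of the important change (threshold = 1), because Table 1 records FEV1 in % and no threshold is given.

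**Model.** Individual change is Normal with mean m and SD s.
- Improved share = P(change ≥ +1) = 1 − Φ((1 − m)/s).
- Worsened share = P(change ≤ −1) = Φ((−1 − m)/s).

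**Case A: half the decline prevented.** Mean −0.8 without the programme and −0.4 with it. For s = 1, improved is 1 − Φ(1.8) = 3.6% against 1 − Φ(1.4) = 8.1%. Worsened is Φ(−0.2) = 42.1% against Φ(−0.6) = 27.4%.

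| SD | Difference in improved | Difference in worsened | Improved ÷ worsened |
|---|---|---|---|
| 1 | 4.5 points | 14.6 points | 31% |
| 1.5 | 6.0 points | 10.2 points | 59% |
| 2 | 5.8 points | 7.8 points | 74% |

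For each additional improver in the denominator of ratio (3), the programme also prevents 14.6/4.5 = 3.2, 10.2/6.0 = 1.7 or 7.8/5.8 = 1.3 important worsenings that the ratio leaves out.

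**Case B: all of the decline prevented.** Mean −0.8 without and 0 with the programme.

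| SD | Improved, without / with | Difference | Worsened, without / with | Difference |
|---|---|---|---|---|
| 0.5 | 0.0% / 2.3% | 2.3 points | 34.5% / 2.3% | 32.2 points |
| 1 | 3.6% / 15.9% | 12.3 points | 42.1% / 15.9% | 26.2 points |
| 2 | 18.4% / 30.9% | 12.4 points | 46.0% / 30.9% | 15.2 points |

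With full prevention of a decline of 0.4, 0.8 or 1.2 thresholds and SD 0.5, 1 or 2, the improved share moves by 2.0 to 17.3 points and the worsened share by 7.4 to 63.3 points. The improved share moved less in all nine combinations.

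**Case C: benefit confined to patients who would have declined.** Suppose worsened falls from 40% to 20%, stable rises from 50% to 70%, and improved stays at 10%. The improver difference is exactly 0, so ratio (3) has a zero denominator. The worsened share would show the effect with 82 patients per arm (two-sided 5%, 80% power, no clustering; also assumptions).

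**Reading.** That stable and worsened patients score alike follows from the definition and needs no assumption. The loss of sensitivity does depend on assumptions. It is large when SD is small against the threshold or when only decliners benefit, and moderate when individual change varies widely.

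**The case against.** The strongest reply is that the evaluation does not rest on this count. Changes in outcome measures are compared between programmes and against controls, so a smaller fall in FEV1 can be seen there. Flare-ups, SF-36, EQ-5D, QALYs and cost per episode prevented all credit prevention, and exacerbations are a listed COPD outcome. The article claims comparability of the clinical outcomes only to some extent, and ratio (3) is one of four given as examples. Uncertainty in the ratios is handled by bootstrapping, cost-effectiveness planes and acceptability curves. The course of lung function over two years is not stated, and thresholds are commonly left to the full plan.

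Most of this stands, and it rules out three stronger conclusions that a reader might infer:
- **That clinical success as a whole is defined only as improvement.** The measures just listed contradict this.
- **That a programme which prevents decline scores little or nothing, with a ratio (3) denominator near zero.** Case A gives 4.5 to 6.0 points, or one additional improver per 17 to 22 patients. That is attenuation. Zero needs the special pattern of Case C.
- **That programmes for declining diseases will be ranked lower.** The article states no ranking rule.

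The reply does not rescue the count itself. Raw changes in different clinical measures are on different units, which is why the article introduces a common expression. It also says that the nature and impact of episodes differ by disease. Bootstrapping describes uncertainty in the chosen effect, but prevented worsening stays off the effect axis.

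**Conclusion.** The point holds for two specific items in the Data analysis section: the cross-project expression of the primary clinical outcomes and example ratio (3). Both treat stable and worsened patients alike. For measures that may decline, with lung function in 5 of 22 programmes as the clear candidate, they are less sensitive to prevented deterioration than a count of important worsening.

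Under Case A the improved share shows 31% to 74% of the contrast seen in the worsened share. Other assumptions give larger or smaller losses. These figures rest on a Normal model and on assumed decline, SD and threshold, none of which the article gives. They also presuppose that the measure declines at all, which the article does not say. Other outcomes compensate in part, so this weakens one stated comparison and one ratio. It does not undermine the evaluation as a whole.

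**What to change.** In the Data analysis section, classify every patient in every programme as importantly improved, stable or importantly worsened. Use the same symmetric rule for all measures (the same threshold in both directions) and report all three categories in the cross-project comparison. Beside ratio (3), add the cost per additional patient with important worsening prevented, where there is a comparator. In the delayed-start programmes the controls wait only one year, so that contrast is available at T2 and not at T4.

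Do not change the favourable direction by disease within the single yardstick, for example by scoring COPD on absence of worsening and lipids on improvement. In Case A with SD 1, that would count 100 − 42.1 = 57.9% of COPD patients as favourable without any programme (72.6% with it), against 3.6% and 8.1% improved. The imbalance would be reversed and comparability lost.

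The cost is small: slightly more analysis and reporting, and thresholds fixed before the data are seen. The patient-record values already planned at T0, T2 and T4 are sufficient.

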### Research methods

The study is a practical clinical trial because it addresses questions about the risks, benefits, and costs of DMPs as they would occur in routine clinical practice [15]. Moreover, it combines qualitative and quantitative research methods [19]. The application of a previously developed evaluation model will allow us to determine the relationships between interventions and outcomes [5]. Such a design will yield empirical evidence on the effects of the DMPs as well as reveal effective aspects of the programme and care process changes. Furthermore, it will give insight in working DMPs and demonstrate which elements of the intervention are potentially (cost-) effective. Hence, it will be possible to uncover opportunities and threats to the implementation of DMPs.

The main comparison will be between DMPs, but most have a pre-post test design within them. Seven DMPs have a control group of patients for whom the intervention will be postponed by a period of 1 year (late starters). General practices (clusters) will be assigned to an early starter (intervention) group or late starter (control) group (see figure 2). Two DMPs concerned with eating disorders and stroke will assign patients at random to the comprehensive DMP or usual care.

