A comprehensive investigation at the individual and organisational levels requires multi-level analyses, incorporating variables at different levels of aggregation to differentiate between compositional and contextual effects. Analysis of the outcomes at T1, T2, T3, and T4 will take the dependency of outcomes within patients into account. Multi-level models will be used to distinguish between project- and patient-level effects [26]. The hierarchical structure of the data gives us the opportunity to test the effects of the interventions with respect to structural and process characteristics. Success and failure factors such as the culture of the participating organisations and relational coordination (e.g., communication patterns) are likely to relate to the effectiveness of specific interventions. Multi-level analyses will enable us to test such contextual effects across DMPs.

We will analyse the study's qualitative data - interview transcripts, project documents, and non-participant observation notes - with Atlas.ti. We will use open coding to be alert to issues emerging from the data and if necessary collect additional data to follow themes. Coding will be done by two researchers to increase reliability.

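### In the seven early/late-start programmes the unit of assignment, the general practice, is missing from the named model levels, so standard errors for that contrast are too small if outcomes cluster by practice

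*Protocol article*

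**What the plan says.** The Research methods section of the protocol article describes the controlled part of the study: "Seven DMPs have a control group of patients for whom the intervention will be postponed by a period of 1 year (late starters"). It then gives the unit of assignment: "General practices (clusters) will be assigned to an early starter (intervention) group or late starter (control) group". Two further programmes are handled differently: "Two DMPs concerned with eating disorders and stroke will assign patients at random to the comprehensive DMP or usual care". The same section says that the main comparison is the one between programmes.

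The Data analysis section plans to compare changes in outcome "between DMPs and within programmes between intervention and controls", so the practice-assigned contrast is a planned effect comparison. On dependency, the section makes three statements:

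- A general one: "A comprehensive investigation at the individual and organisational levels requires multi-level analyses, incorporating variables at different levels of aggregation".
- One on repeated measures: "Analysis of the outcomes at T1, T2, T3, and T4 will take the dependency of outcomes within patients into account".
- One on the levels: "Multi-level models will be used to distinguish between project- and patient-level effects [26".

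For the economic analysis it says: "Uncertainty around cost-effectiveness will be dealt with by bootstrapping costs and health outcomes". The resampling unit is not given. No practice level, cluster-robust variance or cluster bootstrap is named anywhere in the article.

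**The concern.** The article defines a cluster and assigns the intervention to it, then names model levels that leave that cluster out. Patients of one practice share staff, organisation and case mix, and the interventions partly work by changing how practices organise care. Some correlation within practices is therefore plausible.

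If that correlation exists and is not modelled, the early-versus-late comparison treats patients of one practice as independent. Its confidence intervals are then too narrow and its tests reject too often. Most programmes have only a before-after design. Of the 7 + 2 = 9 programmes described as having concurrent controls, seven are exposed to this problem. An analysis plan that followed the stated levels would carry the problem forward into programme-effect claims meant for decision makers.

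**Working it through.** **Inputs from the article.** The unit of assignment is the general practice, in 7 of 22 programmes. The named levels are project and patient, with repeated measures within patient. The article states no ICC, patients per practice, practices per programme or significance level, so there is no figure of its own to reproduce.

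**Inputs assumed here.** Practice ICC ρ = 0.01 to 0.05; m = 10 to 50 evaluated patients per practice; nominal two-sided level 5%.

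**Step 1: why the project level does not help.** Write a patient's outcome as project effect + practice effect + patient residual, with total within-project variance σ² and a share ρ of it between practices. Take k early and k late practices of m patients each within one project. The project effect is the same in both arms and cancels from the difference in means. What remains is

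Var(true) = (2/k) × [ρσ² + (1 − ρ)σ²/m] = (2σ²/(km)) × [1 + (m − 1)ρ].

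A model without a practice level uses about 2σ²/(km). The ratio is the design effect DE = 1 + (m − 1)ρ. The true standard error (SE) is therefore about √DE times the model SE, and the actual type I error is about 2 × [1 − Φ(1.96/√DE)].

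**Step 2: numbers.**

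| m | ρ | DE | true SE / model SE | type I error |
|---|---|---|---|---|
| 10 | 0.01 | 1 + 9 × 0.01 = 1.09 | 1.04 | 6.0% |
| 10 | 0.05 | 1 + 9 × 0.05 = 1.45 | 1.20 | 10.4% |
| 20 | 0.01 | 1 + 19 × 0.01 = 1.19 | 1.09 | 7.2% |
| 20 | 0.05 | 1 + 19 × 0.05 = 1.95 | 1.40 | 16.0% |
| 50 | 0.01 | 1 + 49 × 0.01 = 1.49 | 1.22 | 10.8% |
| 50 | 0.05 | 1 + 49 × 0.05 = 3.45 | 1.86 | 29.1% |

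At ρ = 0 the design effect is 1 and the error stays at 5%.

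**Step 3: check by simulation.** There were 4,000 runs per setting with no true effect, and 10 practices per project split 5:5. A patient-level model with project effects was compared with an analysis of practice means within project. At m = 20 and ρ = 0.05:

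- One project: 16.0% false positives without practice, 5.5% with it.
- Seven projects: 16.0% without practice, 4.8% with it.

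The practice-based analysis stayed between 4.3% and 5.5% in every setting tried (m = 10, 20 or 30; ρ from 0 to 0.10). Pooling seven projects does not cure the problem, because the contrast still lies between practices inside each project.

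**The case against.** The strongest reply is that the sentence on levels states a purpose and is not a closed list of random effects. The sentence before it adds within-patient dependency, so the list is already incomplete, and the paragraph also speaks of organisational levels and of the data's hierarchy. The paragraph ends on contextual effects across programmes, while the within-programme comparison appears earlier in the section with no model attached. On that reading, the article merely leaves the variance structure of the contrast open, as a condensed article may.

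Part of this stands. A practice level is not excluded, and the link between the model and the contrast has to be inferred. But the organisational wording is made specific only as project and patient, and no other model is offered for the contrast. The article does not stay silent on levels: it names them and omits the unit that it has just called a cluster.

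Other points limit the scope:

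- A reader might infer that the bootstrap resamples patients independently. The article does not say so. It gives no resampling unit, so this is a matter for clarification and not an error.
- A reader might infer that the study's main conclusions are compromised. The main comparison is between programmes, and the two patient-randomised programmes are not assigned by practice.
- The late starters' delay is one year, and the questionnaires at T1 and T3 cover utilisation only. For quality of life, the contrast with not-yet-treated patients is therefore essentially the one at T2.
- Adjustment for starting values may lower the residual ICC. A pooled model with a random project-by-treatment effect could absorb part of the practice variance, but no such term is stated.

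**Conclusion.** The point holds for the early-versus-late comparison in the seven practice-assigned programmes. An analysis with the stated levels understates the standard errors of that contrast whenever the practice ICC is above 0.

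The direction follows from the design; the size does not. The range of 1.04 to 1.86 for the SE ratio, and of 6% to 29% for the type I error, rests wholly on the assumed ICCs and cluster sizes. The lower end is minor. The upper end would mean nominal 95% intervals that cover about 100 − 29 = 71% of the time. It would go too far to say that the standard errors are certainly wrong by a known amount, because the article supplies neither an ICC nor a cluster size.

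**What to change.** For the early/late-start comparisons in these seven programmes, state that general practice enters the model as a level between patient and programme, or that cluster-robust inference by practice is used. Add a small-sample correction suited to the outcome type and to the number of practices. One correction will not serve every outcome: degrees-of-freedom methods for linear mixed models, such as Kenward-Roger or Satterthwaite, do not fit the planned counts of patients with a clinically important improvement. For consistency, state that the cost-effectiveness bootstrap for these programmes resamples practices.

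This needs a practice identifier kept in the data set and a change of wording; it needs no extra patients or measurements. The price is wider intervals and, where a programme has few practices, possibly unstable variance estimates. The number of practices per programme should therefore be reported beside each result.

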### Integration of findings

Methodologically, the assessment of a DMP is the evaluation of a complex mixture of interventions at the patient, professional and organisational levels. Therefore, qualitative and quantitative methods are mixed throughout all phases of the project from the design stage through data collection and interpretation. This enables understandings of (1) the mechanisms through which DMPs produce change, (2) the contextual conditions necessary to trigger such mechanisms, and (3) the effects of DMPs with respect to context and triggered mechanisms.

Intermediate results of the qualitative, quantitative, and economic analyses will be continually fed back within the research group to improve the 'mixed' character of the study, and enable recognition of emerging themes across research methods and a more fine-grained analysis of data. This is especially relevant in the qualitative component of the project. The quantitative data will be revealed to the qualitative researcher to allow him or her to tailor the interviews and observations accordingly. Although each researcher has responsibility for a particular part of the study, regular team interaction will ensure optimal integration of the results of the different study parts.

